#### 6.5.1.4.2 *Eligibility and Recruitment for Managerial IDIs*

IDIs participants must be: ≥18 years of age; a DHMT member (or designee), a CFL site-level supervisor (or equivalent), or a district-, regional-, or national-level CFL programme manager (or similar); and generally familiar with PMTCT/ HIV services available in the relevant district(s). We will exclude any potential IDI participant if they are unwilling or unable to provide written informed consent. A standard invitation letter will be sent initially to potential participants, followed by a phone-call and/or in-person visit to explain the study. Where interested and available, a date and venue convenient to the participant will be identified.

##### 6.5.1.4.2.1 *Consent Procedures for Managerial IDIs*

Participation in the IDIs will be completely voluntary and subject to written informed consent in English. Interviewers will make it clear that participants do not need to answer questions that make them feel uncomfortable. All those taking part in managerial IDIs will receive the Malawi Kwacha equivalent of \$10, and a snack and/or refreshment for their participation.

##### 6.5.1.4.3 *Data Collection for Managerial IDIs*

A small team of trained study interviewers will conduct all IDIs using semi-structured discussion guides that will explore general domains of feasibility and implementability, including: *implementation and fidelity* (the extent to which CFL models are delivered according to program objectives and work plans in challenging field contexts and offer comprehensive services); *practicality* (how are CFL models managed, and to what extent do CFL models complement or duplicate existing systems and activities with other partner health projects and MOH programs and clinics); *adaption* (the extent to which CFLs model function in different settings like clinics, communities, homes, etc.); *integration* (the ease with which CFLs model are integrated within the existing health system); and *expansion* (the perceived ease with which a CFL model, or its components, can be scaled up or become owned by government). Within this thematic framework, questions will be open-ended to allow the moderator to probe for emerging and minor themes. IDIs will last approximately 60 minutes each.

All IDIs will be audio-recorded and then transcribed verbatim. IDIs will be conducted in English given that participants are professional managerial staff. The audio-recordings will not be marked with any identifying information. Digital audio-recordings will be stored on a password-protected computer,

accessible only to trained study staff. After transcription, audio recording will be stored for a maximum of 2 years and then destroyed.

#### *6.5.1.4.4 Additional Procedures for Managerial IDIs*

Interviewers will be trained and mentored by the study investigators on IDI procedures, IDI standard operating procedures (SOPs), and use of standardized discussion guides.

## **6.5.2 Study Procedures for Objectives 2 & 2a**

### **6.5.2.1 Objectives 2 & 2a Overview**

In “real-world” PMTCT programmatic settings where the absolute numbers of MIPs is large, prospectively ascertaining clinical outcomes, including maternal viral load and infant/young child HIV status, is often challenging for an implementation research study such as this one. Therefore, we will learn about MIP health outcomes using an efficient, two-stage cohort design.

In the first stage, we will retrospectively construct a cohort of HIV-infected women entering the national PMTCT program and receiving community-facility linkage (CFL) services or the SOC between July 1, 2016 and June 30, 2017 in our 40 randomly selected facility catchment areas. For all areas, we will review existing, routine MOH data for all eligible women and their infants to abstract retrospective data on our outcomes of interest—12-month maternal retention in care, viral suppression for HIV-positive mothers, and 12-month infant HIV-free survival. (Of note, maternal and infant outcomes have two different “starting points” for determining the 12-month outcome, which we will account for in our analysis—in the case of HIV-positive mothers the “starting point” is ART initiation date and for infants it is date of birth).

In the second stage, we will use epidemiological sampling to obtain outcomes on a nested cohort of approximately 1,200 randomly selected MIPs drawn from the full retrospective cohort (*see section 6.4 Sample Size*). Information will be collected from these 1,200 participating MIPs through a detailed questionnaire and blood sampling for maternal viral load and infant HIV testing, and will be enriched by qualitative in-depth interview (IDI) data for 60 women purposively selected from among the MIPs in the nested cohort. IDIs will explore maternal perceptions, experiences, and satisfaction with CFL models and services, including with their key components, and how these services have affected their longitudinal engagement with and retention in the national ART program.

Data from the first and second stages will be combined to present the HIV care cascade for MIPs in aggregate, and by CFL model/ SOC, from HIV testing through ART initiation and viral suppression. Uptake of HIV services at the three main steps of the HIV care cascade will be calculated according to UNAIDS definitions and compared against established “90-90-90” benchmarks (*see section 7.2.2.2 below*).

#### **6.5.2.2 First Stage Data Collection: Chart Review**

In the first stage of data collection, we will seek out outcome information for all MIPs in the full retrospective cohort by abstracting existing clinical and demographic data from routine MOH treatment cards and registers and from electronic medical records (where available) at our 40 selected facility catchment areas. Study staff will have no direct contact with MIPs in the retrospective cohort, apart from those MIPs selected to potentially participate in the nested cohort.

Information to be abstracted will include such data as: HIV testing history, 6-, 12-, and 24-month post-ART initiation maternal vital status (e.g. alive in care, transferred out, stopped ART, died, and lost to follow-up); 6- and 24-month maternal viral load (timing per national guidelines); exposed-infant first HIV-1 DNA PCR result (from 6 weeks of age per national guidelines); 12- and 24-month HEI vital status (including death); and 12- and 24-month HEI HIV sero-status (timing per national guidelines). We will also abstract the first documented DNA PCR test result for all HEIs from HCC registers and treatment cards and laboratory records, which will include results for samples taken at 6 weeks of age and later, including “late” test results for HEIs who enrolled into follow-up after 6 weeks of age. Similarly, many HIV-exposed children undergo their 12- and 24-month rapid tests after these time points due to late presentation to clinic for “milestone” visits, HIV test kit stock outs, and other reasons. As a result, the “median age at first HIV rapid testing” may be closer to 15 or 18 months than the recommended 12 months, providing valuable information about HEI HIV status at or near the conclusion of breastfeeding. Because HEIs enrolling into routine HIV care through June 30, 2017 are eligible to join the full retrospective cohort, some HEIs will not reach age 24 months before administrative censoring (anticipated to take place between end 2017 and end 2018, depending on the district). The 12-month calendar period for cohort construction was selected to maximize power for the primary outcome (i.e. 12-month maternal HIV retention in care). 24-month outcomes for infants who are censored before reaching age 24 months will be represented by those who are observed at age 24 months and by a simple sensitivity analysis (*see section 7.0 Data Analysis*).

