## 6.0 Methodology

### 6.1 Study Design Overview

We propose to rigorously define and compare three widely adopted models for community-facility linkage with each other and the standard of care using a mixed methods approach involving both quantitative and qualitative data collection.

For the quantitative component, we will first use stratified random sampling to select facility catchment areas in 5 Malawi districts where implementing partners have focused PMTCT programming. We will then visit each selected area to construct a retrospective cohort of HIV-infected women who entered the national PMTCT program and received CFL services or the SOC between July 1, 2016 and June 30, 2017. These dates have been chosen to align with the latest change to Malawi HIV guidelines supporting universal “test and treat” strategy, which became national policy on April 1, 2016 and reached stable rolled out on July 1, 2016. Using existing data, we will gather individual-level retrospective data on each woman and her infant from PMTCT enrolment through the child’s second birthday. Next, we will enrich these data using an epidemiological sampling method designed to overcome the limitations traditionally associated with retrospective data (e.g. missing data, outcome misclassification, etc.). In this second stage, we will randomly select a sample of women from our full

cohort to create our nested cohort. These women will complete a questionnaire about their experiences with CFL models and services, undergo viral load testing, and have their children ages 12–24 months receive HIV testing. Such prospective data collection will enable us to confirm primary outcomes, fill in missing data, and improve study data quality more generally.

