## 6.3 Study Population

We will begin our study by reviewing existing data from a generalizable sample of women (and their infants/ young children) from selected facilities in the 5 districts meeting the following eligibility criteria:

- Newly diagnosed or having documented evidence of HIV infection between July 1, 2016 and June 30, 2017 in selected health facilities;
- Documented referral to or enrolment in Malawi's PMTCT/ ART program;
- Pregnant (at any gestational age) or breastfeeding at the time of HIV diagnosis/ positive HIV status identification;
- $\geq 16$  years of age at the time of PMTCT referral/ enrolment (includes adults and emancipated minors according to Malawi law);
- Received Antenatal or PMTCT services at a facility catchment area served by a CFL model of interest or SOC.

Existing, routine data for these women and their infants will form the basis for our full retrospective cohort. From these data, we will randomly select women and their infants (i.e. mother-infant pairs) to participate in the nested cohort.

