#### 6.4 Sample Size

After enumerating the full retrospective cohort, we will randomly select eligible HIV-positive women and their HEIs for our nested cohort. For this nested cohort, our sample size will be determined by a power calculation for our primary outcome of interest—maternal retention in care 12 months after ART initiation. For this calculation (*see summary in Table 2 below*), we assume that 75% of MIPs receive services from a CFL model of interest in our selected districts, and that approximately 73% of HIV-positive mothers receiving the SOC will be retained in care at 12 months post-ART initiation (based on the most recent, first quarter 2017 data from the Malawi national program). With a two-sided alpha of 0.05, we will have 80% power to detect a programmatically meaningful 8% difference in the proportion of mothers retained in care between those who do and do not receive CFL services by enrolling 894 mothers from CFL sites and 298 mothers from SOC sites into our nested cohort (for a total of 1,192 mothers). Assuming that approximately 75% of HIV-positive mothers in SOC sites will be virologically suppressed (a weighted composite of 88% suppression among the 73% of HIV-positive mothers in care and approximately 40% suppression among the 27% of HIV-positive mothers not in care), we will have 83% power to detect a 8% difference in the proportion of HIV-suppressed mothers between those who do and do not receive CFL services. Finally, assuming that we will enrol about one HEI for every mother in the nested cohort, and that 92% of all HEIs not receiving CFL services (i.e. receiving SOC) are alive and HIV-free at 12 months (based on published data that 7% of HEIs become HIV-infected by 12-months and 96% of HIV-exposed but *uninfected* infants are alive at 12 months), we will have 90%

power to detect a 5% difference in HIV-free survival between HEIs who do and do not receive CFL models of interest by recruiting 1,192 total HEIs..

| Table 2: Summary of power and sample size calculations for primary outcomes of interest. |                                 |                    |              |                                 |                                 |

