#### *6.5.2.3.2 Selecting Patients for Potential Nested Cohort Participation*

All women meeting eligibility criteria for the retrospective cohort will be eligible for random sampling and inclusion in the nested cohort, regardless of their ART status in the national program (i.e. regardless of whether they are known to be active and in care or defaulted/ lost to follow-up). At each study site, we will enumerate a complete list of study-eligible PMTCT clients from the full retrospective cohort in chronological order of the date of their PMTCT referral/ enrolment. For relatively small enumeration lists (e.g. containing fewer than approximately 50—70 clients), all clients will be included as potential participants. For larger enumeration lists, we will randomly select every second to  $n^{\text{th}}$  PMTCT client for potential participation in the nested cohort, with the interval depending on the total number of eligible mothers at the site from which to choose at least 30 participants (e.g. if there are 80 mothers available for sampling, we will select every second entry; if there are 200 mothers available for sampling we will select every fourth entry; etc.). We will continue this selection process until we enrol at least 30 nested cohort participants at each study site. It is possible that we are unable to complete study procedures (described in detail below) on the first MIPs selected at each site. In such a case, we will continue randomly sampling from the enumeration list until we reach at least 30 consenting MIPs who have completed study procedures in fulfilment of our site-based enrolment target.

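### Section 6.5.2.2 gives infants their own entry date of 30 June 2017, which conflicts with the sections that bring infants in through mothers who may be pregnant up to that same day

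*Protocol*

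**What the plan says.** **Mothers.** Protocol 6.3 admits women under two criteria that matter here: "Newly diagnosed or having documented evidence of HIV infection between July 1, 2016 and June 30, 2017 in selected health facilities" and "Pregnant (at any gestational age) or breastfeeding at the time of HIV diagnosis/ positive HIV status identification". It then states: "Existing, routine data for these women and their infants will form the basis for our full retrospective cohort". No date is set for the infant.

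**Pairs.** Section 6.1 says "we will gather individual-level retrospective data on each woman and her infant from PMTCT enrolment through the child’s second birthday". Section 6.5.2.1 has routine data reviewed for all eligible women and their infants. Section 6.4 sizes the infant comparison by "assuming that we will enrol about one HEI for every mother in the nested cohort". Section 6.5.2.3.2 says "All women meeting eligibility criteria for the retrospective cohort will be eligible for random sampling and inclusion in the nested cohort".

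**Infants.** Section 6.5.2.2 alone gives the infant a date: "Because HEIs enrolling into routine HIV care through June 30, 2017 are eligible to join the full retrospective cohort". This is offered as the reason why some infants will not reach 24 months before administrative censoring. The next sentence speaks of a 12-month calendar period for building the cohort.

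**Denominator.** Section 7.2.2.1 takes 12- and 24-month HIV-free survival as proportions of all infants enrolled in an HEI birth cohort. That cohort is not defined anywhere else.

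**The concern.** The maternal window and the infant date in 6.5.2.2 close on the same day. For a woman identified while breastfeeding this causes little difficulty, because the infant already exists. For a woman identified while pregnant, the infant enrols in HIV care only after the remaining weeks of pregnancy plus whatever time passes before registration.

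Take a woman who enters at 20 weeks in mid-March 2017. She is eligible under 6.3 and due about early August 2017. Under 6.3 and 6.1 her infant belongs to the cohort; under the date in 6.5.2.2 it does not. A data abstractor has no rule for choosing between them.

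The choice sets the denominator for the infant outcomes, one of which (12-month HIV-free survival) has a power statement in Table 2. A cut-off would not remove infants at random. It would keep those whose mothers entered while breastfeeding, late in pregnancy or early in the window, and drop those whose mothers entered earlier in pregnancy and late in the window. Inclusion would then be tied to how much antiretroviral treatment the mother could have had before delivery. The mix could differ between community-facility linkage (CFL) models, though the protocol has no figures on this.

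**Working it through.** **1. The plan's own figure.** Section 6.4 and Table 2 state 90% power for infant HIV-free survival, 92% versus 97%, with 298 standard-of-care and 894 CFL infants, two-sided alpha 0.05. A two-proportion normal approximation with continuity correction gives:

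- pooled proportion = (298 × 0.92 + 894 × 0.97)/1,192 = 0.9575
- SE under the null = √(0.9575 × 0.0425 × (1/298 + 1/894)) = 0.01349
- SE under the alternative = √(0.92 × 0.08/298 + 0.97 × 0.03/894) = 0.01672
- corrected difference = 0.05 − ½(1/298 + 1/894) = 0.04776
- power = Φ((0.04776 − 1.96 × 0.01349)/0.01672) = 89.9%

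This reproduces the 90%. Without the correction the result is 92.1%. The corrected formula also gives 80.1% for retention (stated 80%) and 82.6% for suppression (83% in the text).

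**2. Share of infants after the date, if it is a cut-off.** The entry window is 365 days, or 52.14 weeks. Three inputs are assumptions: even maternal entry over the window, gestational age at entry, and infant age at enrolment in HIV care. Section 6.5.2.2 mentions 6 weeks, but as the age for the first DNA PCR, not for enrolment. With delivery at 40 weeks:

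share = (40 − gestational age at entry + infant age at enrolment) / 52.14

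| Gestation at entry (weeks) | Infant enrolled at birth | Infant enrolled at 6 weeks |
|---|---|---|
| 12 | 28/52.14 = 54% | 34/52.14 = 65% |
| 16 | 24/52.14 = 46% | 30/52.14 = 58% |
| 20 | 20/52.14 = 38% | 26/52.14 = 50% |
| 24 | 16/52.14 = 31% | 22/52.14 = 42% |
| 28 | 12/52.14 = 23% | 18/52.14 = 35% |
| 32 | 8/52.14 = 15% | 14/52.14 = 27% |

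These are shares of pregnant enrolees' infants. The split between pregnant and breastfeeding entrants is not given either. If, for illustration, 80% entered pregnant, the range over all infants would be 0.8 × 15% = 12% to 0.8 × 65% = 52%.

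**3. What that would do to power if nothing replaced the lost infants.** Losing 30% leaves 834 infants and power of about 78% (82% without correction). Losing half leaves 596 and about 63% (70% without). These are conditional figures; see the objection on replacement.

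**4. Follow-up if later infants are included.** A woman who enters at 12 weeks on 30 June 2017 delivers 28 weeks later, about 12 January 2018. Her infant reaches 12 months in January 2019. Section 6.5.2.2 puts censoring between end 2017 and end 2018, so 12 months would be missed. Section 7.2.2.1 puts it between 1 February 2018 and 30 April 2019, so 12 months could be reached in a late-closing district. In a district closing at end 2017, no infant born in 2017 reaches 12 months. Sections 6.5.2.2 and 7.2.2.1 make specific provision only for infants who miss 24 months.

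**The case against.** The strongest reply is that 6.5.2.2 contains no exclusion rule. The clause is the subordinate half of a sentence about 24-month censoring and does not say that only those infants are eligible. Eligibility is set in 6.3, where every criterion applies to the woman and her infant follows. Sections 6.1 and 6.5.2.1 agree, and 6.5.2.3.2 orders the sampling list by the mother's referral or enrolment date. Section 6.5.2.3.6 also plans testing of infants from just over 6 weeks of age, in a protocol dated 3 October 2017. An infant enrolled by 30 June 2017 would be at least three months old by then. That section may simply mirror national guidance, but it does not suggest a cut-off.

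Most of this stands. A reader might infer that infants enrolling later are definitely excluded; the document does not support that. What remains is that 6.5.2.2 uses the language of eligibility, gives the only infant entry date in the protocol, and relies on it as the last entry date to explain missing 24-month data. It cannot be taken literally alongside 6.1, 6.3 and 6.4.

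A reader might also infer that half the infants are lost. That is one cell of the table, needing entry near 20 weeks and enrolment at 6 weeks, and neither is stated. Nor is it shown that the planned 894 and 298 infants would be unavailable. Section 6.5.2.3.2 keeps sampling until at least 30 consenting pairs per site have completed procedures, and Table 3 projects 2,740 to 3,720 mothers for 1,200 places. Some strata have little room (stratum 16 plans 90 mothers from 50 to 100), but no overall shortfall follows. The effect would show as selection more than as a proven loss of numbers.

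**Conclusion.** The point holds as a conflict between sections over who enters the infant cohort. It does not hold as a demonstrated exclusion. If the date in 6.5.2.2 were applied as a cut-off, about 15% to 65% of the infants of pregnant enrolees would fall outside it, given even enrolment, entry at 12 to 32 weeks and infant enrolment between birth and 6 weeks. The documents supply none of these inputs, so the range shows that the share is material and does not estimate it. The direction of any resulting bias, and whether it differs by CFL model, cannot be established from the protocol.

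The secondary infant outcomes are affected; maternal 12-month retention is not. The sentence needs correcting on the milder reading too: once later-born infants are included, some will miss 12 months as well as 24, and two sections give different censoring dates.

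**What to change.** - In 6.3 and 6.5.2.2, state that every live-born infant of an eligible woman's index pregnancy or breastfeeding episode is in the infant cohort, whatever the infant's own date of enrolment in HIV care. Use the same definition for the HEI birth cohort in 7.2.2.1.
- Remove the 30 June 2017 limit on infants from 6.5.2.2.
- Abstract HIV Care Clinic registers and cards up to each district's field closing date.
- Say in 6.5.2.2 that some infants may not reach 12 months before censoring, and treat them as censored in the 12-month analysis.
- Reconcile the censoring dates in 6.5.2.2 (end 2017 to end 2018) with those in 7.2.2.1 (1 February 2018 to 30 April 2019).

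The cost is a few sentences and a longer abstraction range in registers the team already reviews. The downside is more infants with incomplete 12- or 24-month follow-up, so the infant estimates will lean more on the censoring and weighting methods.

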### **6.5.2.3 Second Stage Data Collection**

#### *6.5.2.3.1 Nested Cohort Procedures Overview*

Randomly selected nested cohort MIPs will undergo written informed consent, complete a structured questionnaire about their experiences with CFL models and other health services, and undergo one-time HIV testing (i.e. by collecting a dried blood sample [DBS] from the mother for viral load testing and either performing rapid HIV-1/2 antibody testing or collecting a DBS sample on the HEI for HIV infection ascertainment, as indicated based on HEI age per national testing guidelines).

